**How the planned methods achieve the aim or research questions**

The primary outcome is quality of life as measured by mean scores on the 12-item Short Form Health Survey (SF-12) and the Quality-of-life scale (QOLS). This outcome will be obtained via two online surveys: at baseline (T0) and post intervention (T1).

The secondary outcomes will include anxiety as measured by mean scores on generalized anxiety disorder 7 (GAD-7); depression as measured by mean scores on the patient health questionnaire (PHQ-9); work productivity and activity assessment (WPAI:SHP); pain as measured by mean scores on the visual analogue scale (VAS) and the McGill pain questionnaire (MPQ). These outcomes will be measured via two online surveys at T0 and T1. Questions on participants’ non-pharmacologic therapy preferences and experiences of participating in the trial will also be included, and measured at T0 and T1, respectively. Flexibility as measured by the finger to floor distance (FFD); obesity as measured by mean scores on body mass index (BMI); blood pressure (BP), and oxygen saturation (SpO2) as measured by a pulse oximetry device will also be carried out by the researchers, and these outcomes will be measured before the intervention (T0) and post intervention (T1).

Statistical analysis:

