Descriptive statistics for continuous variables will initially be described by mean and standard deviation (SD) for normal data, and by median and interquartile range (IQR) for non-normal data. Categorical data will be summarised by frequencies and proportions. The primary and secondary outcomes will be assessed following intention-to-treat principles. Linear mixed modelling with unstructured covariance matrix will be conducted to assess changes in outcomes throughout the study. This model allows for the inclusion of missing data in an intention-to-treat analysis without imputations (e.g., last-observation-carried-forward). Post-hoc tests will be conducted on all pairwise comparisons. The analysis will be adjusted for potential confounding factors such as age, gender, education levels and any other potentially relevant variables where data are available. The corrected Akaike Information Criterion (AICc) will be used to assess model fit when covariates are added to the model. Normality assumptions will be assessed using the Shapiro-Wilk test. If required, non-linear transformations such as the square root and log-transformations, will be applied to normalise the data. Statistical significance will be set at an alpha level of 0.05. False discovery rate (FDR). Corrections will be applied to all analysed outcomes to account for multiple comparisons. Effects sizes, defined by partial eta squared, will be reported and interpreted, with 0.01, 0.06 and 0.014, respectively, identified as small, medium and large effects (43). All analyses will be conducted using R version 4.1.

The qualitative data collected via open-ended questions across the two online surveys will be used to help explain or elaborate on the quantitative data. Qualitative data will be analysed using template thematic analysis. Template thematic analysis uses ‘a priori’ code frames to analyse and report on the data. The initial skeleton code frame is often formulated from the questions asked of participants and then built upon during analysis in an iterative process.

Element 2

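### If age, gender and education enter the T0–T1 mixed model as plain main effects, they do not adjust the treatment effect on change; the plan should specify a model in which they do

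*Protocol*

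**What the plan says.** The statistical analysis text in the Protocol (Element 1, under *How the planned methods achieve the aim or research questions*) names one model and its target: "Linear mixed modelling with unstructured covariance matrix will be conducted to assess changes in outcomes throughout the study". On covariates it says: "The analysis will be adjusted for potential confounding factors such as age, gender, education levels", and it leaves the list open to further recorded variables. On how they are judged it says: "The corrected Akaike Information Criterion (AICc) will be used to assess model fit when covariates are added to the model".

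Two further statements bear on the point. The model is chosen partly because "This model allows for the inclusion of missing data in an intention-to-treat analysis without imputations", and "Post-hoc tests will be conducted on all pairwise comparisons".

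The outcomes are measured at two visits only, T0 and T1. The Project synopsis gives 20 participants per group, 40 in total. The text does not state whether covariates enter as main effects or with a time interaction, whether the T0 arm means are free or constrained equal, or which contrast is the treatment effect.

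**The concern.** Age at entry, gender and education do not change over 12 weeks. A covariate simply added to a repeated-measures model gets one coefficient that serves both visits. It explains the level of the score, but it says nothing about change, and change is the stated target. The adjustment would then leave the arm-by-time contrast where it was.

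With 20 per arm, some chance imbalance in age or education is to be expected. A report could describe the effect on change as adjusted for these factors when the fitted model had corrected none of the imbalance. AICc gives no warning, because it rewards covariates that predict level.

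**Working it through.** **Inputs.** From the Protocol: two visits, unstructured covariance, time-constant covariates, 20 per arm. It gives no SD, T0–T1 correlation, effect size, power or dropout rate, so it has no figure to reproduce here. Step 1 needs none of these. The sizes in the later steps rest on the assumptions stated there.

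**Step 1: algebra.** Let g be arm and z the covariates.

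- Y0 = a0 + b0·g + c·z + e0
- Y1 = a1 + b1·g + c·z + e1
- D = Y1 − Y0 = (a1 − a0) + (b1 − b0)·g + (e1 − e0)

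The term c·z cancels from D. With an unstructured 2×2 covariance the likelihood factors into f(D given g) × f(Y0 given D, g, z), and the two factors share no constrained parameters. The arm-by-time effect b1 − b0 appears freely in the first factor only. Its estimate is therefore the raw difference in mean change, whatever z is.

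**Step 2: numerical check, complete data.** Ten simulated trials of 20 v 20 were fitted by REML (assumed: residual SD 10, correlation 0.6, three prognostic covariates, true effect 5). One of them:

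| Model | Estimate | SE |
| --- | --- | --- |
| Raw difference in mean change | 6.343 | – |
| Change contrast, no covariates | 6.343 | 2.812 |
| Change contrast, covariate main effects | 6.343 | 2.812 |
| Change contrast, covariate-by-time terms | 5.055 | 2.660 |
| T1 contrast, no covariates | 5.135 | – |
| T1 contrast, covariate main effects | 5.525 | – |

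Over the ten trials, main effects left the change estimate equal to the raw difference to about 1e-13 and the SE unchanged to about 4e-7 (optimiser tolerance). Covariate-by-time terms moved the change contrast by 0.43 on average (maximum 1.29). Main effects moved the T1 between-arm contrast by 0.65 on average (maximum 1.65).

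A separate worked data set of 40 agrees. The change contrast was 0.586911 (SE 0.244998) both without and with the covariates, and 0.495 with covariate-by-time terms. A T1 model gave 0.620 with T0 only and 0.554 with T0 and the covariates.

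**Step 3: missing T1.** In the ten trials, the change estimates with and without covariate main effects differed by 0.20 on average (maximum 0.52) with 10% of T1 missing, and by 0.18 (maximum 0.48) with 20% missing. This small movement is not the intended adjustment. A further simulation (600 trials per setting; assumed residual SD 1, correlation 0.6, covariate correlating 0.3 with change, T1 missing at random) measured how far the estimated effect follows chance covariate imbalance, as a slope:

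| T1 missing | No covariates | Main effects | Covariate-by-time |
| --- | --- | --- | --- |
| 0% | 0.280 | 0.280 | 0.003 |
| 10% | 0.322 | 0.325 | 0.050 |
| 20% | 0.268 | 0.268 | −0.011 |

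Main effects removed essentially none of the dependence on imbalance. Covariate-by-time terms removed nearly all of it.

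**Step 4: size of what is left.** A standardised covariate differs between arms with SE √(2/20) = 0.32 SD. If it correlates 0.3 with change (assumption), a 1-SE imbalance shifts the estimate by 0.3 × 0.316 = 0.09 SD of change, and a 2-SE imbalance by 0.19 SD.

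**Step 5: AICc.** In 4,000 simulated trials with a covariate that predicts level only (coefficient 0.4, assumption), AICc retained it in 92%, although the change contrast cannot move.

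**The case against.** The strongest reply is that the Protocol does not state the model that fails. It mentions neither main effects only nor free T0 means, and it never names the arm-by-time contrast. A SAP that is not shown could settle these details, and the sentence as written is compatible with the fix below. This stands as a limit: the point is conditional on the ordinary reading of adding a covariate. It does not remove the point, because the Protocol already commits to a model, a target of change and an adjustment, and the default way of combining them leaves that target unadjusted.

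A reader might infer something stronger: that the adjusted effect always equals the unadjusted difference in mean change exactly, so that no adjustment takes place. The documents do not support that.

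- Exact equality needs complete data, and the Protocol picks this model partly in order to keep participants with missing values.
- The planned pairwise comparisons include the between-arm contrast at T1, which the covariates do change. The hypothesis, that quality of life is better in the Tai Chi group than in the control group, can be read as that contrast.
- With T0 means constrained equal, which the text leaves open, covariates do act. In the ten trials they moved the estimate by 0.38 on average (maximum 0.80). In the worked data set it hardly moved (0.620 to 0.619), while the SE fell from 0.237 to 0.207.

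Two points about harm also stand. Under randomisation the unadjusted change contrast is unbiased, so the 0.09 SD above is the error given a particular imbalance, not systematic bias. And the Protocol plans no display of adjusted beside unadjusted results, so a false show of robustness is a possibility only.

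**Conclusion.** The concern holds in conditional form. If age, gender and education enter as main effects with free T0 arm means, they leave the change contrast and its SE unchanged with complete data, and the estimate nearly unchanged with modest T1 dropout. The adjustment then does not act on the treatment effect on change, although it does alter the between-arm contrast at T1. The algebra rests only on that model form and complete T0–T1 data. The sizes (about 0.2 points of movement under dropout at SD 10, 0.09–0.19 SD of change left uncorrected, 92% AICc retention) rest on the assumed values given. What is at stake is precision and chance-imbalance error in a trial of 40. It is worth correcting before analysis because a better method uses data already collected.

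**What to change.** Replace the adjustment sentence with one that defines the effect: the treatment effect is the arm difference at T1 from a linear model of the T1 score on arm, T0 score, age, gender and education.

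The alternative is to keep the mixed model and add a covariate-by-time term for each named covariate. This is a different estimator, since it does not condition on the T0 score (0.495 against 0.554 in the worked data set), so one of the two must be chosen in advance. In either case, report the unadjusted contrast beside it, and do not take AICc retention as evidence that the effect has been adjusted.

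**Cost.** One sentence of wording and a few degrees of freedom. For k covariate columns unrelated to change, the SE of the change contrast rises by a factor of about √((38 − 1)/(38 − k − 1)), where 38 = 40 − 2. With k = 3 this is √(37/34) = 1.04, matching the simulated 1.04. With three education levels, k = 4 gives √(37/33) = 1.06. If one of three covariates correlates 0.4 or 0.5 with change, the simulated SE ratio is 0.96 or 0.91, a gain of 4–9%. The T1 model uses only participants with a T1 value; the mixed model with covariate-by-time terms keeps those with T0 alone.

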| **Outcome measures and time points:**  The outcomes are QoL as measured by mean scores on the 12-item Short Form Health Survey (SF-12) and the EuroQoL (EQ-5D); anxiety as measured by mean scores on generalized anxiety disorder 7 (GAD-7); depression as measured by mean scores on the patient health questionnaire (PHQ-9); work productivity and activity assessment (WPAI:SHP) questionnaire; pain as measured by mean scores on the visual analogue scale (VAS), and the McGill pain questionnaire (MPQ). These outcomes will be measured via two online surveys prior to (T0) and post-intervention (T1). Questions on participants’ non-pharmacologic therapy preferences and experiences of participating in the trial will also be included, and measured at T0 and T1, respectively.  In addition to these self-reported questionnaires conducted via online surveys, objective measures will also be carried out by the research team at ECU Holistic Health Research Clinic, which is in the university’s Sport Centre where the Tai Chi/Qigong training program take place. These measures include flexibility as measured by the finger to floor distance (FFD); obesity as measured by mean scores on body mass index (BMI); Vital signs (blood pressure, heart rate, respiratory rate, temperate, and oxygen saturation) as measured by a blood pressure monitor, tympanic, and pulse oximetry device. These outcomes will be measured prior to (T0) and post-intervention (T1). People diagnosed with pre-diabetes or diabetes, their HbA1C and fasting BGL will also be measured via test kits at T0 and T1. | |
| **Sample Size:** Based on previous Tai Chi/Qigong exercise intervention studies, n = 20 participants will be required per group (total n=40) for this study. | |

Element 1

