**Benefit of exploring these research questions**

Several studies demonstrated that Tai Chi/Qigong has many health benefits, such as decreased heart rate, decreased blood pressure, lowered lipid levels, decreased levels of stress hormones, enhanced immune function, and improved physical wellbeing and psychological wellbeing. However, there is no consolidated conclusion for Tai Chi/Qigong and more studies in this field are required to provide updated evidence. Therefore, this study aims to address this knowledge gap.

We hypothesize that Quality of life (QoL) in Tai Chi/Qigong group is better than the control group (usual care). We hope that the results of our research can be used to inform our knowledge about how to better manage chronic diseases that many Australians are suffering.

There are no foreseeable risks associated with this research project.

**Outline the design of this research; its methods and details of the instruments to be used to collect the data, including psychometric properties if applicable.**

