**PICOs:**

**P:** Adults aged 18 years and older will be recruited for this trial

**I:** 12-week Tai Chi/Qigong exercise + usual care

**C:** Waiting list control with usual care (e.g., other exercise)

**O:**

The primary outcome is quality of life as measured by mean scores on the 12-item Short Form Health Survey (SF-12) and the EuroQoL (EQ-5D). This outcome will be obtained via two online surveys: at baseline (T0) and post intervention (T1).

The secondary outcomes will include anxiety as measured by mean scores on generalized anxiety disorder 7 (GAD-7); depression as measured by mean scores on the patient health questionnaire (PHQ-9); work productivity and activity assessment (WPAI:SHP); pain as measured by mean scores on the visual analogue scale (VAS) and the McGill pain questionnaire (MPQ). These outcomes will be measured via two online surveys at T0 and T1. Questions on participants’ non-pharmacologic therapy preferences and experiences of participating in the trial will also be included, and measured at T0 and T1, respectively. Flexibility as measured by the finger to floor distance (FFD); obesity as measured by mean scores on body mass index (BMI); blood pressure (BP), and oxygen saturation (SpO2) as measured by a pulse oximetry device will also be carried out by the researchers, and these outcomes will be measured before the intervention (T0) and post intervention (T1).

**S:** This is a single-blind (assessors blind to group allocation), double-armed, randomised controlled trial on the therapeutic effect of a 12-week Tai Chi/Qigong exercise for adults.

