**How will formal recruitment of potential participants be conducted?**

The study will involve providing participants with a 12-week Tai Chi/Qigong exercise.

Participants who fulfil our inclusion and exclusion criteria will be assigned with a unique identification number and provided with a Participant Information Letter outlining what will be involved in the trial and an online survey starting with a consent form. People who gave consent will complete the online survey after ticking a box under the online consent form.

Participants who completed the online survey will be invited to ECU sports centre where the 12-week Tai Chi/Qigong exercise take place, the researcher team will carry out the baseline physical assessments (e.g., FFD, BMI, BP, and SpO2).

Following the completion for the baseline measurements, the participants will be assigned to either a control or treatment group, with the assistance of a blinded statistician, via a randomised block design. This ensures the sample number in each group remain relatively similar through the recruitment process until the quota is reached.

Element 3

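### One FDR correction over all analysed outcomes makes the primary quality-of-life verdict depend on the secondary p-values

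*Protocol*

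**What the plan says.** The PICOs section defines the primary endpoint: "The primary outcome is quality of life as measured by mean scores on the 12-item Short Form Health Survey (SF-12) and the EuroQoL (EQ-5D"). Under the heading on how the planned methods achieve the aim, the second primary instrument is the Quality-of-life scale (QOLS) instead of the EQ-5D. The only stated hypothesis concerns quality of life.

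The secondary outcomes in both sections are GAD-7, PHQ-9, WPAI, pain VAS, McGill pain questionnaire, finger-to-floor distance, BMI, blood pressure and SpO2. The synopsis, which assigns no tiers, adds heart rate, respiratory rate and temperature, and for a subgroup: "People diagnosed with pre-diabetes or diabetes, their HbA1C and fasting BGL will also be measured via test kits at T0 and T1".

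The statistical analysis text says that primary and secondary outcomes are both analysed by intention to treat. It then states: "Statistical significance will be set at an alpha level of 0.05". A detached mention of FDR follows, and then: "Corrections will be applied to all analysed outcomes to account for multiple comparisons". No hierarchy, tier or exemption is given. The synopsis sets the sample size: "n = 20 participants will be required per group (total n=40) for this study". Its only stated basis is earlier studies of the same kind of exercise.

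**The concern.** A primary outcome is named so that the main claim rests on a test whose error rate and power are known in advance. Placing it in one FDR family with every secondary outcome gives that up. The p-value it must reach then depends on how many other measures are analysed and how they turn out. Null secondaries make the rule stricter for the primary; strongly responding secondaries relax it towards an unadjusted 0.05 test for each instrument. With 40 participants there is little power to spare, and nothing in the sample-size statement allows for the correction.

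The family is also not a fixed list. The PICOs section and the synopsis give different sets of measures, and the second primary instrument differs between sections, so the same data could give different primary verdicts under different counts.

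**Working it through.** **Inputs.** From the protocol: 20 per group (synopsis, Sample Size); alpha 0.05 and FDR over all analysed outcomes (statistical analysis text); two primary instruments (PICOs). Assumed, because not stated: Benjamini-Hochberg (BH) as the procedure, two-sided tests, no dropout, and a two-sample t test standing in for the mixed-model group contrast, with d the standardised effect on that contrast.

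**The plan's own figure.** The 20 per group cannot be reproduced, since no effect size, SD or power is given. Solving backwards:
- 80% power, normal approximation: d = (1.960 + 0.842) × √(2/20) = 0.89. The noncentral t gives 0.91.
- 90% power: d = (1.960 + 1.282) × √(2/20) = 1.03, or 1.05 by the t.

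The check uses d = 0.909, which has 80% power unadjusted. This is a reference point, not a figure from the protocol.

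**Family size m.** PICOs: SF-12 and EQ-5D (2) plus nine secondaries = 11. Adding heart rate, respiratory rate, temperature, HbA1c and fasting glucose from the synopsis gives 11 + 5 = 16. These count instruments; counting SF-12 and blood pressure as two variables each would raise both totals by 2.

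**How the verdict depends on the rest.** BH rejects the k smallest p-values, where k is the largest rank with p(k) ≤ 0.05k/m. Suppose the primary p is 0.02.
- m = 11: k must be at least 0.02 × 11/0.05 = 4.4, so at least 5 of the 11 outcomes must be rejected together (cut-off at rank 5: 0.0227).
- m = 16: 0.02 × 16/0.05 = 6.4, so at least 7 of the 16 (cut-off at rank 7: 0.0219).
- If nothing else is rejected, the primary needs p ≤ 0.05/11 = 0.0045 or p ≤ 0.05/16 = 0.0031. Power at those cut-offs is 45.4% and 40.4%.

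**Simulation** (20 per arm, 20,000 replicates, correlation 0 and 0.4; Monte Carlo standard error at most √(0.25/20,000) = 0.35 points). Approximate power for one primary instrument, against 80% unadjusted; responding outcomes all have d = 0.909:

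| What truly responds | m = 11 | m = 16 |
| --- | --- | --- |
| One primary instrument only | 46–47% | 40–42% |
| Both primary instruments, no secondary | 52% | 46% |
| Both primary instruments and four secondaries | 65–67% | 59–61% |
| Everything | 74–77% | 74–77% |

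**Other effect sizes** (m = 13, both primary instruments responding, ranging over the number of responding secondaries and correlation):

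| d | Unadjusted | BH within the primary pair | BH over all outcomes |
| --- | --- | --- | --- |
| 0.5 | 34% | 27–28% | 9–19% |
| 0.8 | 69% | 65–67% | 36–62% |
| 0.909 | 80% | 77–79% | 49–76% |
| 1.2 | 96% | 95–96% | 81–96% |

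**Error in the other direction.** With both primary instruments null and every secondary at d = 1.5, pooled BH declares at least one primary instrument significant in about 8–9% of trials. BH within the pair gives about 5%. With the secondaries at d = 0.909 the pooled figure is about 6–7%. The ceiling for two independent tests is 1 − 0.95² = 9.75%.

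**The case against.** **The reading is not certain.** The FDR wording is broken across two sentences and comes after a plan for post-hoc pairwise tests, so a correction within each outcome is conceivable. It is less natural, because the sentence names outcomes as what is corrected. The naming of the procedure may properly be left to a statistical analysis plan, and its absence is not counted here. The scope of the family, however, is stated in the protocol.

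**A single FDR family is a legitimate, conservative choice.** It is not an arithmetic error, and BH adapts: responding secondaries give back much of the lost power. The protocol's rationale cites benefits on heart rate, blood pressure and psychological wellbeing, so all-null secondaries is a pessimistic case. That stands, and it is why the cost is given as a range.

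**Two stronger readings are tempting.** A reader might infer that the primary loses about half its power. The documents do not support that as a result: they give no effect size, power or number of tests, and a fall from 80% to about 40% needs 16 measures with only one quality-of-life instrument responding and everything else null. A reader might also infer that the primary test has no 5% error control. BH never rejects a p-value above 0.05, so each instrument taken alone stays at or below 5%. The excess arises only if significance on either of two instruments counts as success, which the protocol leaves open.

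**The longer list may not be in the family.** The synopsis assigns no tiers, so its five extra measures are not shown to belong. That stands as well; 11 is the firmer count and 16 an upper case by instrument.

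**Conclusion.** The concern holds as a cheap improvement to a stated rule. Followed as written, the plan lets the secondary p-values help decide the primary verdict, in a trial that names one primary outcome and states one hypothesis. Pooling under BH can never give the primary more power than an unadjusted 0.05 test. At d about 0.91 it keeps about 40–52% (secondaries null), 59–67% (both primary instruments and four secondaries responding) or 74–77% (all responding), against 80%. In relative terms that is a loss from (80 − 40)/80 = 50% down to (80 − 77)/80 = 4%. The either-of-two false-positive chance can reach about 8–9%.

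These figures rest on BH, two-sided t tests, 20 completers per arm, a family of 11 to 16 measures and an effect size chosen for reference. The direction of the power effect needs none of the assumed effect sizes; its size does.

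**What to change.** 1. Reconcile the second primary instrument between the PICOs section (EQ-5D) and the section on how the methods achieve the aim (QOLS).
2. Test the primary outside the secondary family, in one of two ways: one named primary variable at two-sided 0.05, or both instruments with a correction within that pair only, stating whether success needs either or both.
3. Apply FDR only to one fixed list of secondary outcomes, reconciled between the synopsis, the PICOs section and the methods section. How the subgroup-only HbA1c and fasting glucose are reported is the sponsor's choice, provided the list says whether they count.

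This costs a few sentences and no participants. The price is that either one quality-of-life instrument becomes secondary, or the pair carries a small correction: about 77–79% power per instrument against 80% when both respond at d about 0.91, and about 70–72% if only one does.

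### The only effect size the protocol defines, partial eta squared, is unsigned and varies with each instrument's retest correlation, so its size labels do not track the between-arm difference

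*Protocol*

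**What the plan says.** The statistical analysis paragraph (Protocol, Element 1, under the heading on how the planned methods achieve the aim) sets the model: "Linear mixed modelling with unstructured covariance matrix will be conducted to assess changes in outcomes throughout the study". It then fixes the effect measure, "Effects sizes, defined by partial eta squared, will be reported and interpreted", and the labels, "with 0.01, 0.06 and 0.014, respectively, identified as small, medium and large effects". No mean difference, standardised mean difference or other effect size is defined elsewhere in the protocol.

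The same paragraph plans descriptive means and SDs (medians and IQRs for non-normal data). It also states "Post-hoc tests will be conducted on all pairwise comparisons" and "Statistical significance will be set at an alpha level of 0.05", with false discovery rate correction, and it allows square-root or log transformation where needed.

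The section on the benefit of the research states the hypothesis with a direction: "We hypothesize that Quality of life (QoL) in Tai Chi/Qigong group is better than the control group (usual care". The synopsis gives 20 participants per group, and outcomes are measured at two times, T0 and T1.

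**The concern.** An effect-size label should say how far the arms differ, and which arm did better. Partial eta squared is a share of variance. It cannot be negative, so it cannot answer whether quality of life is better rather than merely different.

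When the contrast is a change from T0 to T1, the error term is the variation of within-person change, and that shrinks as the two visits correlate more strongly. The measure therefore mixes the size of the difference with the stability of the instrument. The protocol applies one set of labels to quality-of-life, anxiety, depression and pain scores, flexibility, BMI, blood pressure and oxygen saturation. If these differ in retest correlation, the same standardised difference can be called by different names, and a table of labels would partly rank instruments by their stability.

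**Working it through.** **Inputs from the protocol.** n = 20 per arm; two time points; printed cut-offs 0.01, 0.06 and 0.014. The protocol gives no expected value of partial eta squared, so there is no figure of its own to reproduce.

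**Assumptions, not in the protocol.** Group-by-time contrast; complete data; equal SD at T0 and T1; true between-arm difference d = 0.5 SD; T0–T1 correlation r from 0.3 to 0.8.

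**Formulas.** The variance of a change score is 2(1 − r) in SD² units. With two arms of 20:

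- t² = d² / [2(1 − r) × 2/20] = 0.25 / [0.2(1 − r)] = 1.25 / (1 − r)
- partial eta squared = t² / (t² + 38), where 38 = 40 − 2

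| r | t² | Partial eta squared | Label if *large* is read as 0.14 (assumption) | Label as printed, 0.014 tested first | Label as printed, bands in numerical order |
|---|---|---|---|---|---|
| 0.3 | 1.79 | 0.045 | small | large | large |
| 0.5 | 2.50 | 0.062 | medium | large | medium |
| 0.7 | 4.17 | 0.099 | medium | large | medium |
| 0.8 | 6.25 | 0.141 | large | large | medium |

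The range is about threefold (0.141 / 0.045 = 3.1). In the other direction, the difference needed to reach 0.06 is d = √[(0.06/0.94) × 38 × 4(1 − r)/20]. That is 0.58 SD at r = 0.3, 0.49 SD at r = 0.5 and 0.31 SD at r = 0.8.

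**Sign.** d enters only as d², so −0.5 SD gives the same values as +0.5 SD. Simulation of 20,000 trials per setting agrees: medians for benefit and harm are 0.046 and 0.047 at r = 0.3, 0.062 and 0.063 at r = 0.5, and 0.142 and 0.144 at r = 0.8.

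**Comparison with a signed difference.** The difference divided by the T0 SD is +0.50 (or −0.50) at every r. The correlation shows where it belongs, in the precision. The standard error is √[2(1 − r) × 2/20], which is 0.374 at r = 0.3 and 0.200 at r = 0.8. The 5% critical F on 1 and 38 df is 4.098, so the t multiplier is √4.098 = 2.024. Treating the SD as known, the 95% intervals around 0.50 are about −0.26 to 1.26 and 0.10 to 0.90.

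**The case against.** The strongest reply is that little is lost. Group means, the coefficients of the fitted model and the pairwise comparisons all show which arm did better, and the significance decision rests on the corrected tests, not on the labels. This stands. A reader might infer that the trial would report no direction and nothing in score units; the protocol does not support that, because the descriptive statistics and post-hoc comparisons supply both.

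A reader might also count the absence of a stated confidence interval as an omission. Reporting format is commonly left to a statistical analysis plan, which may exist, so that is not the point here. The point is the measure that the protocol does define.

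A third stronger reading is that a mixed model cannot yield partial eta squared, or that the choice of degrees of freedom makes it arbitrary. With two visits and complete data, the unstructured-covariance group-by-time test equals the two-sample t-test on change scores, and F/(F + 38) is the exact ANOVA value. Using 76 residual df (80 observations − 4 parameters) would turn F = 4.10 from 0.097 into 0.051, but in this setting that is a faulty conversion, not an equally valid one. The protocol names no df method, which matters mainly if data are missing. The argument above does not need it.

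The missing sign and the shifting labels are separate effects. The missing sign gives benefit and harm the *same* label; only the correlation makes labels differ. Labels change only when a cut-off is crossed: with 0.014 tested first, 0.5 SD is *large* at all four correlations. Even under that reading a smaller difference can move: 0.25 SD gives 0.0116 (*small*) at r = 0.3 and 0.0162 (*large*) at r = 0.5.

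Finally, the protocol gives no retest correlations, so it cannot be said which of its instruments would be favoured.

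**Conclusion.** The point holds as an improvement to the defined effect measure. It does not show a wrong figure, and it does not affect the validity of the tests. Under the stated assumptions, one 0.5 SD difference spans 0.045 to 0.141 and can fall on either side of the 0.06 cut-off, and benefit and harm of equal size cannot be told apart by value or label. The exact values depend on the assumed correlations; the dependence on correlation and the lack of sign do not.

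The sentence also prints the *large* cut-off (0.014) below the *medium* one (0.06). That is a separate error, and putting the cut-offs in order would leave the present point unchanged.

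**What to change.** In the statistical analysis paragraph, replace the effect-size sentence with wording such as:

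> *For each outcome the treatment effect will be the model-based Tai Chi minus control difference in T0–T1 change, reported with its 95% confidence interval in the units of the instrument. For untransformed outcomes the signed difference divided by the pooled T0 SD will also be given. Where an outcome was transformed for analysis, the effect will be back-transformed. Size will be interpreted from these estimates and intervals. Partial eta squared may be given as a supplementary figure without size labels.*

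The baseline-adjusted difference at T1 is an acceptable alternative, provided that one contrast is named and used throughout, because the two differ when baselines differ. After a log transformation the back-transformed effect is a ratio of geometric means (for a contrast in change, the ratio of the two arms' T1-to-T0 ratios). A difference on the square-root scale has no single back-transform, so the fitted arm means should be back-transformed and shown beside the contrast.

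The cost is a few sentences of protocol wording. The same fitted model supplies the estimates, with no extra data or participants. The downsides are a back-transformation step for transformed outcomes and less direct comparison with papers that report only partial eta squared; keeping it as a supplement limits the latter.
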